### Randomization

Randomization to the intervention group or control group will be performed at the patient level. A co-author who is not involved in data collection or analysis will use a random sequence generator (http://www.random.org) to allocate patients in a random sequence to the intervention or control group. In a separate room after completion of the baseline measurements, an independent researcher will tell individual participants to which group they have been allocated. If this is the intervention group, the researcher will help them install and unlock the app on their smartphone, and will also provide information on how to use it. To identify dental plaque during the intervention period, participants in the intervention group will receive twelve disclosing tablets (Gum® Red-Cote®). To prevent treatment contamination, adolescents in the control group will not have access to the intervention, as the app will be locked with a personal code that will only be provided to the adolescents in the experimental group.

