In the next part of the registration process, which is intended to help adolescents identify their dental plaque levels, they will be asked to use the disclosing tablets and to take a selfie of their teeth on which dental plaque is visualized by the disclosing tablet. The participant has to fit the selfie into a fixed window, upon which the app will superimpose a grid. The adolescent will then be asked to register the amount of plaque by clicking the disclosed areas in the grid. The app will interpret the number of clicks (i.e. absence or presence of plaque). Then, on the basis of this plaque assessment and of the answers to the questions on oral-health procedures during the registration phase, the app will provide feedback. If the adolescent has complied with the oral-health recommendations and if dental plague is absent, positive reinforcement will be given. If the adolescent has not complied with these recommendations or if dental plaque is present, personal oral-health advice will be given in short videos and a peer model (i.e. an adolescent with fixed orthodontic appliances) will demonstrate how to clean teeth with fixed appliances. Adolescents will then set a particular goal with regard to tooth-brushing frequency and duration, the use of a proxy brush and/or fluoride mouth rinse (goal-setting). Next, they will be required to formulate when and where they will perform the oral-health behavior (formulating “if-then” goals or an implementation intention). As part of the implementation planning, the app will provide an option for setting reminders for oral-health-behavior tasks. The action plans formulated will be saved on the main page of the app. At the end of the installation process, the app will encourage adolescents to use the brushing timer daily and to monitor their oral-health behavior by registering in the app whether they have performed their tasks.

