Every day throughout the 12-week intervention period, push-notifications will be sent instructing adolescents to use the app to enter whether or not they have accomplished their daily dental activities, and to remind them to use the brushing timer when brushing their teeth (at installation, adolescents set the time at which they would like to receive this notification). When adolescents decide to brush, they have the option of turning on the timer. As well as showing the time elapsed during brushing, the timer supports good tooth brushing by showing where and how to brush according to the 5-step method. When adolescents have completed brushing, the app provides positive reinforcement.

Each week, adolescents will be asked via the app to evaluate their dental plaque levels and review their behavioral goals. For this purpose, they will use a disclosing tablet to visualize the dental plaque. They will also be asked to take a selfie of the result and to indicate the visualized dental plaque (following the same procedure as in the registration phase). On the basis of the information both on the selfie – which indicates an increase or decrease in the number of clicks and thus the amount of plaque – and on the activities performed that week, the app concludes whether the adolescent’s goals have been attained. It then compliments the adolescent for using the app, and, if necessary, helps him or her to set new goals or to adapt the existing ones. If adolescents have failed to attain their goals, they can formulate coping plans, i.e., “if-then” plans specifying how they can deal with difficult situations. To establish these, they use volitional sheets, i.e., sheets with pre-established difficult situations and solutions, such as “If I’m too tired to brush my teeth in the evening, then I’ll brush my teeth right after dinner.” These coping plans will be saved on the main page of the app, so adolescents will be reminded of them when they open the app.

If the adolescent does not use the app, it will send personalized text-messages every three days reminding them to use it. These messages will be based on information obtained during installation of the app. For example, “Brushing will help to keep your teeth healthy and beautiful.”

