#### Modified Silness and Loë plaque index

A systematic review conducted by Al-Anezi concluded that the modified Silness and Loë plaque index by Williams (1991) is the most valid and discriminatory index for measuring plaque accumulation in orthodontic patients [35, 36]. Using a mouth mirror and a probe, we will therefore use this index to establish the amount of plaque on the buccal surfaces of the first premolars, canines and incisors. According to the position of the orthodontic bracket, the buccal surface of each tooth is divided into four zones, i.e., those mesial, distal, gingival and incisal to the bracket [35, 36]. Each of the four sites of the buccal tooth surface is given a score from 0 to 3, where 0 indicates the absence of plaque; 1 indicates no plaque visible, but an accumulation of soft deposit on a probe when used to clean the surface; 2 indicates a moderate accumulation of soft deposit on the tooth which can be seen with the naked eye; and 3 indicates an abundance of soft matter on the tooth. For the analysis, values are summed to obtain a total score per participant.

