#### Process evaluation

A process evaluation will be performed to examine intervention fidelity (i.e., the extent to which participants comply with the intervention); and participants’ experiences with the intervention program, including the perceived effectiveness of various components of the WhiteTeeth app.

Information on intervention fidelity will be collected through the app. For medical-ethical reasons, the app users’ data will not be uploaded automatically. Instead, participants will have to send it themselves from their smartphone to the database. During intervention allocation, participants will be informed about the collection of their users’ data, and will be asked to send it via the app each week. At 6 and 12 weeks follow-up, all participants will be reminded to send their user’s data via the app. User’s data consists of (1) the week that the users’ data is sent, (2) the login code of the app, (3) the total number of selfies, (4) the total number of clicks on the selfie, (5) the total number of times that the brushing timer is opened, (6) the average number of minutes brushed registered by the brushing-timer, (7) the action plans that are entered into the application, (8) the goals that were set, (9) the number of times that they watch a video about (I) dental plaque and cleaning their teeth either with (II) a manual toothbrush, an (III) electric toothbrush, or (IV) interdental brushes; and (10) their initial motives for cleaning their teeth.

At 12 weeks follow-up, the participants’ experiences with the intervention program will be examined in a short questionnaire consisting of open and closed questions (See Additional file 4 for questionnaire part III).

To maximize retention of participants, all participants will receive a letter at baseline on the importance of adhering to the intervention and on participation in the follow-up measurements. To promote their active participation in the study, participants will receive monetary compensation (€10) at the end of the trial.

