### Data-management

All data will be recorded using FileMaker Pro© 15 database. Separate FileMaker Pro forms have been designed for both the clinical measurements and the questionnaires.

The researchers will register clinical data on tablets. To fill in all questionnaires, participants will use the tablets in a separate room. To ensure that appropriate help and guidance can be given when needed, this will be done in the presence of one of the researchers. To minimize data-entry errors, the forms have inbuilt check-and-skip rules. FileMaker Pro will allow us to export the data safely from tablets to SPSS Statistics database. For participants who withdraw from the trial, any data collected up to the withdrawal date will be retained and included in the analyses.

Names, mobile phone numbers and addresses will not be recorded in the same forms as sensitive data. Each participant will be given a unique identification number. Each participant will send their weekly user’s data to a secure server owned by ACTA University. Only the principal and the co-principal researchers will have access to the participants’ personal data. All data will be saved on password-protected computers and tablets. When the study has been completed, all personal identifiers will be deleted. Data will be kept in stored digitally at the coordinating center (ACTA) for 5 years after completion of the study.

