### Blinding

The participants in this study cannot be blinded for the intervention allocation after randomization. To ensure the blindness of assessors and clinicians, the principal researcher will ask the participants not to communicate with outcome assessors or their clinicians on whether they use the app.

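### Nothing in the text keeps the app arm's weekly plaque staining, or the app-related visit tasks, apart from the blinded plaque scoring at T1 and T2

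*Protocol article*

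**What the plan says.** **Staining.** Under Randomization, twelve red disclosing tablets go to the intervention group only, and the app is installed after the baseline measurements. In the section on the WhiteTeeth app, staining first occurs at registration, where "they will be asked to use the disclosing tablets and to take a selfie of their teeth". It then recurs: "Each week, adolescents will be asked via the app to evaluate their dental plaque levels and review their behavioral goals". The means is stated next: "For this purpose, they will use a disclosing tablet to visualize the dental plaque". The app is for home use, and no day or hour is fixed for the check.

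**Scoring.** Outcomes are collected at T0, week 6 (T1) and week 12 (T2). The Data collection section puts the questionnaire first, then the clinical measurements, then the check-up. On the plaque index, "1 indicates no plaque visible, but an accumulation of soft deposit on a probe when used to clean the surface", while score 2 is a moderate deposit that the naked eye can see.

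**Blinding.** The measure given for keeping assessors and clinicians blind is that "the principal researcher will ask the participants not to communicate with outcome assessors or their clinicians on whether they use the app".

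**App-related tasks at the same visits.** Process evaluation says: "At 6 and 12 weeks follow-up, all participants will be reminded to send their" app-use data. It also places a questionnaire on experiences with the intervention at week 12. Data-management says of questionnaire completion that "this will be done in the presence of one of the researchers", and that researchers register the clinical data.

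**The concern.** A dye that colours plaque is supplied to one arm and used at a weekly interval, while plaque is scored by eye and probe at multiples of that interval. Two things could follow if a participant stains shortly before a visit.

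- **Unblinding.** Residual dye would tell the assessor which arm the participant is in. A request for silence does not touch this.
- **A one-arm shift in the plaque score.** Dye could make deposit easier to see and push a site from 1 to 2. Alternatively, staining could prompt cleaning just before the visit and lower the score. Neither reflects the lasting oral hygiene that the trial means to compare.

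The reminder and the experience questionnaire raise the same blinding question by another route: they concern the app, they fall at scoring visits, and the text does not say whether they come before or after scoring. At stake is the plaque index, a co-primary outcome and the basis of the sample size.

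**Working it through.** **1. Calendar.** With installation at T0, weekly checks fall nominally on days 7, 14, ..., 84. Check 6 is day 6 × 7 = 42, which is T1. Check 12 is day 12 × 7 = 84, which is T2. These are nominal days only.

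**2. Tablets.** Registration plus 12 weekly checks makes 1 + 12 = 13 stainings, against 12 tablets. At one tablet per staining, the supply covers registration and weeks 1 to 11. A week-12 staining is therefore supplied only if an earlier check was skipped or a tablet was split. If registration counts as the first weekly check, the twelfth falls at week 11. Week 6 is fully supplied under every reading, and T1 enters the mixed model for the overall effect (Statistical analysis section).

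**3. What the stated safeguards cover.**

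| Safeguard | Section | Covers dye at T1/T2? |
|---|---|---|
| Sequence made by a co-author outside data collection and analysis | Randomization | No |
| Allocation told in a separate room, after baseline, by an independent researcher | Randomization | No |
| Questionnaires in a separate room | Data collection, Data-management | No |
| Request not to mention app use | Blinding | No |

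**4. The reminder.** It is worded for all participants, but Randomization says that controls cannot open the app. Taken literally, the two sections conflict. Taken as meaning app users, it is an arm-specific task at a scoring visit.

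**5. Size, as an illustration.** The plan's own figure first: n = 2 × (1.960 + 0.842)² × 0.7² / 0.35² = 62.8, so 63 per arm, as stated. It does not depend on this point.

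With 63 per arm, SE = 0.7 × √(2/63) = 0.125. Let b be an assumed change in the app arm's mean score, on the scale of the 0.35 target (taken as the 0–3 scale). The observed difference is 0.35 − b, and power is approximately Φ((0.35 − b)/SE − 1.96).

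| Assumed b | Observed difference | Power |
|---|---|---|
| 0 | 0.35 | 80% |
| +0.05 | 0.30 | 67% |
| +0.10 | 0.25 | 52% |
| +0.15 | 0.20 | 36% |

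For a downward shift with no true effect, two-sided rejection is 1 − Φ(1.96 − |b|/SE) + Φ(−1.96 − |b|/SE). This gives 6.9% at b = −0.05 and 12.6% at b = −0.10, instead of 5%.

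An upward dye shift is (share of app users with dye) × (share of their sites moved one point). Assumed shares of 10–20% and 20–40% give 0.1 × 0.2 = 0.02 to 0.2 × 0.4 = 0.08. Neither share is in the documents, and only sites that would otherwise score 1 can make this move.

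**The case against.** The strongest reply is that dye in the mouth at scoring is inferred, not scheduled. The check is weekly, at home, on no fixed day, and check-ups are only approximately six-weekly. The documents do not say how long dye lasts. Score 2 needs a moderate deposit as well as visibility, so a thin stained film does not become a 2 by definition. The article also condenses a fuller protocol, and the figure showing the visit procedures is not available.

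Most of this stands, and it rules out several stronger readings that a reader might infer:

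- That staining is due on the scoring days at both visits. The text fixes no day, and the tablet count makes week 12 the weaker case.
- That a definite share of the 0.35 target is lost. The range 0.02/0.35 = 6% to 0.08/0.35 = 23% follows only from assumed shares, and the direction is open.
- That dye shifts both primary outcomes. The bleeding index has no plaque-visibility criterion. Only unblinding could reach it.
- That assessors watch participants do app tasks. No section says that the researcher present at the questionnaires scores, or that the reminder or experience questionnaire precedes scoring.
- That the request for silence is the only protection of any kind. Concealment and separate rooms are also stated. It is the only one stated for assessors after allocation.

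What the reply does not remove is that the article names its safeguard for assessors and also describes a weekly, one-arm procedure that this safeguard cannot cover. That is a gap between stated procedures, not merely detail left to another document.

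**Conclusion.** The point holds as a risk that the stated procedures leave open, not as a demonstrated bias. Staining is confined to one arm, recurs weekly, and is not kept away from blinded scoring on an index that depends partly on what can be seen. The overlap is best supported at week 6. The shift argument concerns the plaque index only, and its direction could favour or disfavour the app. Its size is unknown: the power and error rates shown rest on assumed shifts and say only that modest shifts would matter. The reminder's wording conflicts with the controls' lack of app access, and the order of the app-related tasks relative to scoring is not stated. This is a worthwhile, low-cost improvement. If dye is never recorded, its influence cannot be judged later.

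**What to change.** - Instruct app users to do the plaque check due around T1 and T2 only after that visit's clinical measurement.
- Give the data-sending reminder and the week-12 experience questionnaire after scoring, handled by someone who neither scores nor registers clinical data. The order matters because a reminder limited to app users would itself mark allocation.
- Reconcile the reminder's wording in Process evaluation with the statement in Randomization that controls cannot use the app.
- Have assessors record visible dye or suspected allocation at each scoring, and report this by arm descriptively. Do not use it to exclude visits. Dye would occur essentially in one arm and after randomisation, so dropping those visits would select on adherence and depart from the intention-to-treat principle.

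The cost is two selfie checks moved by a short time, a fixed visit order and one tick-box. The sample size does not change.

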### Data collection

Figure 1 presents an overview of the data-collection procedures. Before the orthodontic check-ups at T0, T1 and T2, all participants will fill in a digital questionnaire on the tablet (Ipad® Air 2.0) in a separate room at the clinic. Next, before the orthodontic check-up, the clinical measurements will be made.

#### Demographic or background information

The first part of the self-administered digital questionnaire includes questions on the participants’ demographic background and any possible confounding variables (age, sex, education level, nationality, cultural background, and smoking status (see Additional file 2 for questionnaire part I)). Information will be retrieved from the orthodontic files about the date on which treatment with fixed orthodontic appliances started and about the type of orthodontic bracket (e.g., self-ligating or conventional appliances, and the presence of elastic hooks and/or looped wires).

#### Self-reported oral-health behavior and its psychosocial factors

The second part of the self-administered digital questionnaire contains questions with both single-response and multiple-response items on oral-health behaviors and their psychosocial factors (HAPA factors) (see Additional file 3 for questionnaire part II). This questionnaire was derived from earlier studies on oral health [15, 32–34]. The additional file specifies which questions were derived from which original questionnaire. First, to ensure that the integrity of the content was maintained, the original questions were translated into Dutch and then back-translated to English. Next, to ensure that the questions are comprehensible, the questionnaire was piloted.

The questionnaire asks respondents to report the frequency with which they use a toothbrush, a proxy brush, dental floss, toothpicks, mouth rinse, and other dental aids. It used the following 7-point scale: 1: less than twice a month or never, 2: twice a month, 3: once a week, 4: two to three times weekly, 5: once daily, 6: twice daily, and 7: three times daily or more. For the analysis, these response options will be recalculated to establish the weekly frequencies of each of the oral-health behaviors. Self-reported tooth-brushing frequency and tooth-brushing duration will both be measured in one open question, i.e., “In the last four weeks, how many times have you brushed your teeth per day?” and “How much time do you spend on brushing your teeth at a time?”. For the analysis, these two items will be multiplied to obtain a single item: self-reported tooth-brushing duration (minutes per day).

With regard to the psychosocial factors relevant to tooth brushing and the use of a proxy brush, the questionnaire includes questions on “risk perception”, “action-self-efficacy”, “intention”, “maintenance self-efficacy”, “recovery self-efficacy”, “action control”, “social influences” (including parental support, descriptive and subjective norm), “action planning” and “coping planning”. Next, the questionnaire includes questions on adolescents’ outcome expectancies regarding dental cleaning, and questions about “action-self-efficacy” and “intention” regarding the use of mouth rinse. All psychosocial factors will be assessed on 5-point scales ranging from “very low” (1) to “very high” (5) for risk perception, and from “totally disagree” (1) to “totally agree” (5) for the remaining items. To obtain a single score per psychosocial factor for tooth brushing and the use of a proxy brush, the scores will be summed. The headers in the questionnaire (part II in the Additional file 3) show the items that are summed to generate the score for each psychosocial factor.

#### Clinical measurements

At baseline and at 6 and 12 weeks’ follow-up, the state of adolescents’ oral hygiene will be determined by the amount of plaque and gingival bleeding at the buccal surfaces of the first premolars, canines and incisors. These elements were chosen on the basis of the finding by Chapman et al. (2010) that the maxillary lateral incisor was the tooth most frequently and severely affected by white spot lesions; it was followed by the maxillary canine, premolar, and central incisor [2].

To achieve this, the following clinical assessments will be carried out:

#### Modified Silness and Loë plaque index

A systematic review conducted by Al-Anezi concluded that the modified Silness and Loë plaque index by Williams (1991) is the most valid and discriminatory index for measuring plaque accumulation in orthodontic patients [35, 36]. Using a mouth mirror and a probe, we will therefore use this index to establish the amount of plaque on the buccal surfaces of the first premolars, canines and incisors. According to the position of the orthodontic bracket, the buccal surface of each tooth is divided into four zones, i.e., those mesial, distal, gingival and incisal to the bracket [35, 36]. Each of the four sites of the buccal tooth surface is given a score from 0 to 3, where 0 indicates the absence of plaque; 1 indicates no plaque visible, but an accumulation of soft deposit on a probe when used to clean the surface; 2 indicates a moderate accumulation of soft deposit on the tooth which can be seen with the naked eye; and 3 indicates an abundance of soft matter on the tooth. For the analysis, values are summed to obtain a total score per participant.

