#### Bleeding upon marginal probing (BOMP)

Gingival bleeding will be assessed with the Bleeding on Marginal Probing index (BOMP). This will be used to score the condition of the gingiva according to the method described by Van der Weijden et al. (1991). In summary, a periodontal probe (tapered tine, tip diameter 0.5 mm; Hu-Friedy, Liemen, Germany) runs along the soft tissue wall at the orifice of the pocket – i.e., the marginal gingiva – at an angle of approximately 60° to the longitudinal axis of the tooth [37]. To determine whether probing elicited marginal bleeding (score 1) or not (score 0), we will assess the mesio-vestibular, vestibular, disto-vestibular sections of the vestibular surfaces of the first premolar, canines and incisors. The presence or absence of bleeding will be scored within 30 s of probing. To obtain a total number of bleeding sites per participant, all scores for the analysis will be summed.

To ensure the reliability of the clinical measurements, the clinical examiners at each site (a dentist and student dental hygienists) will be trained and calibrated by an experienced ACTA University examiner two weeks before the start of the study. The calibration will involve a separate group of ten people.

It will not be possible to determine inter-rater reliability by performing the clinical measurements twice, as the first set of measurements will affect the results of the second: plaque will removed by the probe used to determine the plaque score, and more marginal bleeding might be elicited by the second probing of marginal gingiva. For this reason, one examiner will perform the clinical measurements and another examiner will observe them, and then give a second independent judgement. The inter-rater reliability will thus be determined by comparing the scores made by both examiners. This will be done in a random sample of 10% of the measurements. To determine the inter-rater reliability of the primary outcome measures the Intra-class Correlation Coefficients (ICC) will be calculated.

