### Sample size

The sample-size calculation will be based on the primary outcome measure, the modified Silness and Loë plaque index. Between treatment groups we have assumed a 0.35 difference in mean change at week 12 [38]. The required sample size is 2 × 63 patients (setting α = 5% (two-tailed), a standard deviation (s) of 0.7, and the power (1-β) = 0.80) [39]. Allowing for an expected loss of 15%, a sample of 73 patients is needed in each group.

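### The plaque outcome is defined as a participant total, but its target difference of 0.35 and SD of 0.7 fit only an averaged scale; an unadjusted sum also varies with the number of sites scored

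*Protocol article*

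**What the plan says.** In the section on the modified Silness and Loë plaque index, the index teeth are the first premolars, canines and incisors, and each buccal surface has four zones around the bracket. "Each of the four sites of the buccal tooth surface is given a score from 0 to 3". The participant-level outcome follows: "For the analysis, values are summed to obtain a total score per participant".

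The Sample size section uses the same index: "The sample-size calculation will be based on the primary outcome measure, the modified Silness and Loë plaque index". It continues: "Between treatment groups we have assumed a 0.35 difference in mean change at week 12", "setting α = 5% (two-tailed), a standard deviation (s) of 0.7, and the power (1-β) = 0.80". It names no scale for 0.35 or 0.7.

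Bleeding, the other primary outcome, is also a raw sum: "To obtain a total number of bleeding sites per participant, all scores for the analysis will be summed".

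Table 1 (eligibility) asks for fixed appliances in both jaws, bonded at least from premolar to premolar. It does not require all first premolars, or every index tooth, to be present. The article mentions no division by the number of sites scored.

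**The concern.** There are two linked problems.

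1. **Scale.** The endpoint and its target difference appear to be in different units. A reader who is given a group difference on the total cannot set it against 0.35 without guessing a conversion that the article does not supply.
2. **Denominator.** A sum with no denominator mixes cleanliness with the number of sites that could be scored. A patient with fewer index teeth gets a lower total at the same level of hygiene. A site scored at baseline but not at follow-up lowers the total and looks like an improvement.

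The interpretation of a primary outcome is at stake, together with a small loss of precision. The number of patients is not.

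**Working it through.** **Inputs from the article.** Difference 0.35, SD 0.7, two-sided α 5%, power 0.80, loss 15% (Sample size). Four sites per tooth, each scored 0 to 3 (plaque index section). Two first premolars, two canines and four incisors make 8 index teeth per arch, so 16 if both arches are scored.

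**1. The plan's own figure.** n per arm = 2 × (1.960 + 0.842)² × 0.7² / 0.35² = 62.8, so 63, which agrees with the article. Then 63 × 1.15 = 72.45, so 73, which also agrees.

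**2. Range of the total.**
- Both arches: 16 × 4 = 64 sites, maximum 64 × 3 = 192.
- One arch: 8 × 4 = 32 sites, maximum 96.

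**3. Reading 0.35 and 0.7 on the total (64 sites).**
- 0.35 / 192 = 0.2% of the range, or about one third of one grade at a single site.
- An SD of 0.7 on the total is 0.7 / 64 = 0.011 on the site mean. Even if the 64 sites were independent, the SD of change at one site would have to be 0.7 / √64 = 0.0875 on a 0-3 scale. That is not credible.

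**4. Reading them on a 0-3 site mean.** Both are ordinary values. Converted to the total:

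| Sites | Difference | SD | Ratio | n per arm |
|---|---|---|---|---|
| 64 | 0.35 × 64 = 22.4 | 0.7 × 64 = 44.8 | 0.5 | 63 |
| 32 | 0.35 × 32 = 11.2 | 0.7 × 32 = 22.4 | 0.5 | 63 |

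The sample size is the same on every row.

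**5. Dependence on the number of sites.** The number of patients without some index teeth is not given, so the mean site scores and shares below are assumptions.
- Four teeth absent (16 sites) at a mean site score of 0.5, 1.0, 1.5 or 2.0: the total is lower by 8, 16, 24 or 32 points at the same cleanliness.
- One tooth (4 sites) at a mean score of 1.5, scored at baseline but not at follow-up: the total falls by 4 × 1.5 = 6 points with no change in hygiene.
- Bleeding, three sites per tooth: maximum 16 × 3 = 48 with 16 teeth and 12 × 3 = 36 with 12.

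**6. Cost in precision.** Suppose a share p of patients have 12 index teeth (K = 48 sites) and the rest 16 (K = 64), unrelated to treatment. Let the per-site change have SD σ = 0.7 and mean size μ = 0.35 (assumed). With r = E[K²] / E[K]², an analysis of change in the sum needs f = [r(σ² + μ²) − μ²] / σ² times as many patients as an analysis of change in the mean.

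| p | E[K] | r | f | Power at 63 per arm | Mean effect on the total |
|---|---|---|---|---|---|
| 0 | 64 | 1 | 1 | 0.801 | 22.4 |
| 15% | 61.6 | 1.009 | 1.01 | 0.797 | 21.6 |
| 30% | 59.2 | 1.015 | 1.02 | 0.794 | 20.7 |
| 50% | 56 | 1.020 | 1.03 | 0.791 | 19.6 |

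Simulating the baseline-adjusted comparison for the same shares (63 per arm, assumed baseline mean site score 1.5, assumed baseline to follow-up correlations of 0.3 to 0.7) gives a loss of about 0 to 2 power points.

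**The case against.** The strongest reply is that, for patients with all index teeth, the sum is only the mean multiplied by a constant. Sample size, test and p-value are the same, and dividing by the number of sites restores comparability. This stands. A reader might infer that the trial is wrongly sized or powered on a different quantity, and step 4 of the working shows that it is not.

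A reader might also infer that the protocol tells examiners to count absent sites as plaque-free. It does not. That is what an unadjusted sum does arithmetically, and a rule for unscorable sites may exist in a fuller document. What remains is that the summing rule is itself stated, and it carries no denominator.

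It is tempting to set the 24-point gap for a patient lacking four first premolars against the 22.4-point target and call it larger than the effect. That compares one patient's level with a between-group difference in change. Teeth absent at every visit only shrink that patient's change, and randomisation balances them in expectation, so the documents do not support a claim of bias between groups. Nor do they suggest that the set of scored sites shifts much over 12 weeks. Table 1 excludes patients whose appliances are due for removal before the study ends.

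A penalty of 5-11% more patients can be computed, but only for an unadjusted comparison of follow-up totals at a mean site score of 1.5. The Statistical analysis section plans mixed models that control for baseline variables.

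Two limits also stand. Scoring of both arches is inferred: the rationale under Clinical measurements names only maxillary teeth. And bleeding has no sample-size figure to conflict with, so only the denominator argument applies to it.

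**Conclusion.** The point holds as a should-fix. The plaque endpoint as defined is a total on 0-192 (0-96 for one arch), while 0.35 and 0.7 are credible only on an averaged scale. The 0-3 mean per site is the likely one, but this is an inference. If instead a four-zone tooth total (0-12) had been averaged over teeth, 0.35 would be 0.35 × 16 = 5.6 points on the participant total rather than 22.4. The missing scale therefore matters for interpretation.

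The sample size of 2 × 63, or 2 × 73 after loss, stands. The dependence on tooth count is real but small for the group comparison: about 1-3% more patients on change scores and about 0 to 2 power points with baseline adjustment. Both rest on an assumed 15-50% of patients having 12 index teeth and on tooth count being unrelated to treatment. A site that goes unscored between visits would add a false improvement for that patient. The documents give no rate for this.

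**What to change.** - In the plaque index section, define the primary outcome as the mean score per scored site (0 to 3), with the sites scored at that visit as the denominator.
- In the Sample size section, state that 0.35 and 0.7 are on that scale, after checking this against the source cited for the difference.
- In the BOMP section, define bleeding as the percentage of scored sites that bleed, with the sites scored at that visit as the denominator.

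The cost is one sentence per endpoint and one clause in the Sample size section. No measurement is added, because every site is already scored individually; the data forms need only separate a site that was not scored from a score of 0. The number of patients stays the same. The change should be made before the data are analysed.
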